**The following principles will dictate the ablation template**:

The treatment or ablation zone will cover the area of the gland in which the CSPCa lesion(s) (GG ≥2) have been identified by the subject's MRI-TB study as follows:

1. A maximum of 60-75% prostate ablation to include all CSPCa. If the patient has more than one focal lesion on one side, all CSPCa lesions will be destroyed.
2. Treatment may reach the urethra and may cross the midline anteriorly or posteriorly.
3. At least one neurovascular bundle must be avoided by ensuring a minimum distance of ablation zone border to the contralateral neurovascular bundle of 5 mm. If ablation of CSPCa cannot be done without damaging both neurovascular bundles, the patient will not be considered for FT.
4. Up to one redo FT treatment is permissible; if either the protocol’s 6-month MRI-TB result(s) of ablated/treated prostate tissue, or a ‘for-cause’ prostate biopsy (see [section 8.7](#_For_Cause_Tests)) are positive at any point in follow-up.

**The following diagrams illustrate some possible interventions using focal therapy: In each of these scenarios below contralateral nerves were spared.**

[figure not shown]

[figure not shown]

[figure not shown]

[figure not shown]

[figure not shown]

[figure not shown]

[figure not shown]

[figure not shown]

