## Correlative Studies Background

Given this novel combination therapy, we wish to obtain core tissue samples at the time of FT for biospecimen banking and potential future analysis and research on PCa. Two 18-gauge biopsy cores will be collected from the target area(s) and one each from peritumoral and untreated prostate for exploratory outcomes on correlatives during the FT procedure.

At the time of 12-month MRI-TB two 18-gauge biopsy cores will be collected from the ablated area(s) and one each from periablation zone and untreated prostate for exploratory outcomes on correlatives during the FT procedure.

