## Peripheral Blood or Tissue

Collection of Specimen(s):

- One 3mL EDTA tube at screening once eligibility is confirmed and at 6-months after FT

Handling of Specimens(s):

- Normal operating procedures; do not shake or freeze tubes; Label each tube as follows:
  - Clinical trial study number (GU2201)
  - Subject’s (ID) (site number, patient ID example: GU02-01)
  - Date the tube was drawn (example: 2/2/2018)
  - Time of blood draw (example: 15:00)
  - Study time-point (example: Day 1)

Site(s) Performing Correlative Study:

- University of Chicago for long term sample banking.

Shipping of Specimen(s):

- Please refer to relevant SOPs or guidance documents from UC for more details.
- Follow IATA shipping instructions and standards by properly labeling all shipping boxes to prevent delays.
- Attach provided FedEx Airbill to the shipping box.
- Ship per standard operating procedures; Notify [Lab TBD] ***the day of shipping the sample.***
- Samples to be shipped Monday-Thursday only via FedEx Priority Overnight.

Collection of Specimen(s):

- 4 core biopsies of prostate tissue at the time of focal therapy and at 6 month MRI-TB

Handling of Specimens(s):

- Normal operating procedures; Label each as follows:
  - Clinical trial study number using the UChicago
  - Protocol #
  - Subject’s (ID) (site number, patient ID number)
  - Date of collection (example: 2/2/2018)
  - Time of collection (example: 15:00)
  - Study time-point (example: FT)

Site(s) Performing Correlative Study:

- University of Chicago for long term sample banking.

Shipping of Specimen(s):

- Please refer to relevant SOPs or guidance documents from University of Chicago for more details.
- Follow IATA shipping instructions and standards by properly labeling all shipping boxes to prevent delays.
- Attach provided FedEx Airbill to the shipping box.
- Ship per standard operating procedures; Notify University of Chicago ***the day of shipping the sample.***
- Samples to be shipped Monday-Thursday only via FedEx Priority Overnight.

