## Post-Focal Therapy Treatment Efficacy/Surveillance mpMRI and MRI-TB

At 12-months from the time of FT, a SOC mpMRI and MRI-TB will be performed to determine treatment response. Both the imaging study and prostate biopsy results will be used to measure efficacy of the proposed combination treatment. However, if a patient has any other post-treatment biopsy results these may also be used to assess for post-treatment efficacy even if not performed with an mpMRI guided biopsy.

Specifically, an MRI-TB will sample the ablated and unablated prostate tissue to determine if residual CSPCa (GG ≥2) remains in the treated and/or untreated prostate tissue. The mpMRI used for the MRI-TB will follow the same imaging protocol as the pre-treatment study and reported in the same manner. Documentation of the biopsy site(s) will be required. If a new suspicious radiographic lesion(s) is/are detected on the subject’s 12-month mpMRI which was/were not present in the pre-treatment [screening] mpMRI then the targeted biopsy cores of the suspicious area(s) will be obtained. Otherwise, if no suspicious lesions are noted in the 12-month mpMRI then random biopsies from the unablated prostate tissue will be obtained per SOC during the MRI-TB.

- Two 18-gauge biopsy cores will be collected from the ablated area(s) and one each from periablation zone and untreated prostate for biobanking and exploratory outcomes on correlatives.

If the 12-month MRI-TB identifies the presence of CSPCa in the ablated or unablated prostate tissue then the patient will be offered a second treatment with FT (if eligible for such treatments) and the follow-up visits for the re-treatment will be the same as the primary treatment. The patients will stay in the study and will continue to be followed up until 12-months from the first FT procedure. For patients with residual/recurrent cancer who decline or are ineligible for a second FT procedure, one of the whole gland treatments, either radical prostatectomy, whole gland ablation or radiation therapy, will be offered. These data will be recorded as part of report of secondary outcomes. Patients who choose to undergo whole gland treatment during the study follow-up will exit the study at this point. HRQOL surveys, PSA and testosterone levels will be obtained at the exit.

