## For Cause Tests

Clinicians can biopsy the prostate following primary FT if there is a clinically significant rise in PSA (≥2 ng/mL higher from the subject’s post-FT PSA nadir, i.e., ‘for cause’ prostate biopsy) or clinical suspicion for progression of PCa. Nadir value will be defined as the lowest PSA value obtained after completion of combination treatment and recovery to non-castrate levels of testosterone (defined as testosterone levels >50 ng/mL). If there is a concern of prostate inflammation/infection due to a recent biopsy or urinary tract infection, patients will be treated with a course of antibiotics before repeating PSA. If the confirmatory PSA again demonstrates rise of 2 ng/mL above nadir, the patient will be evaluated further for local disease recurrence/progression. A mpMRI will be required prior to the biopsy unless the patient has developed a contraindication to biopsy.

If the untreated area is biopsied, the specimens will be individually identified according to location as determined by a standard protocol.

The specimen will be processed according to standard protocol and examined by a pathologist to note the following features for each core taken.

- Presence of adenocarcinoma
- Grade group
- Length of cancer and total core length

Additional Tests: ‘for cause’ additional tests such as ultrasound, CTAP, BS or PSMA/PET scan will be permissible as SOC practice.

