## Assessment of Disease

Only the treating investigator or qualified designee (MD only) may determine the assessment of disease recurrence or response. Response evaluation will be based on the I-PSS, the SHIM and the EPIC-26, and based upon the subject’s post-FT 6-month mpMRI & MRI-TB.

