**Calendar Footnotes**

1. ADT therapy will consist of any generic luteinizing hormone-releasing hormone agonist which will provide 3-months of treatment (e.g.,.
2. Focal therapy to be completed within 8- to 12-weeks of the initiation of ADT but after the completion of the 8-week mpMRI to allow for it to be used in FT planning.
3. Both adverse events (AEs) and serious AEs and any conmeds to be collected from the time of consent and continuously throughout the study until 30-days after the FT or as indicated in Section 14 of this protocol.
4. Focused abdominal and pelvic genitourinary exam. To be completed once a subject has entered into post-FT follow-up and only as clinically indicated.
5. Vital signs should include: temperature, pulse, respiratory rate, height, weight and blood pressure.
6. Health related quality of life measures including EPIC-26, the I-PSS and the SHIM must be collected at screening. If any of these are not done at screening then these may be completed at Visit 2.
7. PSA collected at “baseline” is defined within eligibility for this protocol. PSA and testosterone value is collected at 3-, 6-, 9- and 12-months post-FT.
8. Screening CBC & CMP, and testosterone must be collected and reviewed for safety within 15-days prior to the initial dose of ADT. Collection at other timepoints only if clinically indicated.
9. A single purple top EDTA tube of 3mL of whole blood to be collected after eligibility is confirmed for banking for future germline testing and at 6-weeks after FT. At the time of FT two 18-gauge biopsy cores will be collected from the target area(s) and one each from peritumoral and untreated prostate. At the time of 6-month MRI-TB two 18-gauge biopsy cores will be collected from the ablated area(s) and one each from periablation zone and untreated prostate.
10. Long term follow-up (LTFU) data collection to begin at 6-weeks after FT and includes collection of any recurrence, re-treatment, survival, and other relevant post-surgical data through 1-year post-FT.
11. FT foley catheter to be removed 1 weeks after FT +/- 3 days.

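### The protocol names a 6-month MRI-TB that it never schedules, and it does not say how a man re-ablated for cancer before month 12 counts in the primary endpoint

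*Protocol*

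**What the plan says.** **Month of the biopsy.** Post-Focal Therapy Treatment Efficacy/Surveillance mpMRI and MRI-TB sets the response biopsy at 12 months after FT. Study Design/Endpoints reads primary endpoints 1 (ablated tissue) and 2 (unablated tissue) at that biopsy. The histology table in Analysis of Primary and Secondary Endpoints is also a 12-month table. In the Study Calendar, MRI-TB is marked only at the 1-year visit, and mpMRI only at week 8 and 1 year.

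Four places say otherwise:

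- Ablation-template principles, item 4 (trigger for a repeat FT): "6-month MRI-TB result(s) of ablated/treated prostate tissue".
- Peripheral Blood or Tissue: "4 core biopsies of prostate tissue at the time of focal therapy and at 6 month MRI-TB".
- Assessment of Disease, which bases response on the "post-FT 6-month mpMRI & MRI-TB".
- Calendar Footnotes, ninth note: "At the time of 6-month MRI-TB two 18-gauge biopsy cores will be collected from the ablated area(s".

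The calendar's correlative-biopsy row also carries a mark at the 6-month visit.

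**Tissue that triggers a repeat FT.** Item 4 names ablated or treated tissue. The post-FT section says that if CSPCa is found "in the ablated or unablated prostate tissue then the patient will be offered a second treatment with FT".

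**Biopsies before month 12.** For Cause Tests provides: "Clinicians can biopsy the prostate following primary FT if there is a clinically significant rise in PSA", or on clinical suspicion of progression. Item 4 allows one repeat FT if such a biopsy is positive at any time in follow-up. The post-FT section keeps re-treated men on study to 12 months from the first FT; only men who choose whole-gland treatment exit. On efficacy it adds: "However, if a patient has any other post-treatment biopsy results these may also be used to assess for post-treatment efficacy". The Missing Data rule imputes a missing post-ablation biopsy as positive and says nothing about a man who was re-treated and then biopsied.

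**The concern.** There are two separate problems.

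The first concerns conduct. Four current texts send sites to a 6-month MRI-TB that the calendar does not contain. One of them rests the assessment of response on it, and two of them direct tissue cores to be taken then. Sites also have two different rules on which tissue justifies a repeat ablation.

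The second concerns classification, and it remains after the month is corrected. A man can have a positive for-cause biopsy at, say, month 8, be re-ablated, stay on study and be negative at month 12. No text makes him a failure. A man with the same biopsy who chooses prostatectomy leaves the study and is a failure, either by that biopsy or by imputation. The primary proportion would then depend on which salvage treatment was chosen. The optional use of other biopsies leaves the choice open until results are known, in a single-arm trial without blinding. The possible error runs one way: a negative reading after a second ablation can lower the observed rate of CSPCa but cannot raise it.

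**Working it through.** **1. The month, side by side.** Correlative Studies Background reads "At the time of 12-month MRI-TB two 18-gauge biopsy cores will be collected from the ablated area(s"; the ninth calendar footnote repeats that wording with 6-month in place of 12-month ("At the time of 6-month MRI-TB two 18-gauge biopsy cores will be collected from the ablated area(s"). The endpoint, procedure, histology table and MRI-TB calendar row all agree on 12 months. The 6-month mentions are therefore stray text, not evidence of a second scheduled efficacy biopsy.

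**2. The plan's own sample size.** Inputs from Sample Size/Accrual Rate: null 0.30, alternative 0.15, alpha 0.05, power at least 80%, 51 men, 10% attrition, 57 in total.

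n = [(z_α√(p0·q0) + z_β√(p1·q1)) / (p0 − p1)]²

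- One-sided: [(1.645·√0.21 + 0.842·√0.1275) / 0.15]² = 49.4, so 50, close to the stated 51.
- Two-sided: 63.9, so 64, which does not match.
- Attrition: 51/0.9 = 56.7, so 57, which matches.

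**3. How many men could be masked.** The protocol gives no rate of for-cause detection or repeat FT, so these shares are assumptions: d = 2–10% of failures re-ablated before month 12, and c = 50–85% of those negative afterwards.

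- Masked share of failures, d·c: 0.02 × 0.50 = 0.010 to 0.10 × 0.85 = 0.085.
- Observed rate at a true 30%, 0.30 × (1 − d·c): 29.7% to 27.5%.
- Men masked of 57: 57 × 0.30 × 0.010 = 0.17 to 57 × 0.30 × 0.085 = 1.45.

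**4. Illustrative effect on a conclusion.** The protocol states no success cutoff, so four are shown. At most 9/51 and at most 11/57 are the largest counts with exact one-sided error within 0.05. At most 8/51 and at most 10/57 are the largest counts whose exact two-sided 95% interval lies below 30% (upper limits 28.6% and 29.9%). Probability of meeting each cutoff at a true 30%:

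| Cutoff | No masking | d·c = 0.010 | d·c = 0.085 | Masked share of failures at which 5% is passed |
| --- | --- | --- | --- | --- |
| ≤9/51 | 3.4% | 3.7% | 7.5% | 4.1% |
| ≤8/51 | 1.5% | 1.7% | 3.7% | 11.6% |
| ≤11/57 | 4.9% | 5.4% | 10.7% | 0.3% |
| ≤10/57 | 2.4% | 2.7% | 5.9% | 6.9% |

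The 0.3% break-even says little, because that cutoff already sits at 4.86% with no masking.

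**5. Offset from imputation.** The 57-man rows assume no missing biopsies. If two of 57 are missing and imputed positive, at most 11/57 requires at most 9 of the other 55. At the largest assumed masking, P(Bin(55, 0.2745) ≤ 9) = 4.0%. With three missing, P(Bin(54, 0.2745) ≤ 8) = 2.2%.

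**The case against.** The strongest reply is that the month error is clean-up, since every text that defines the endpoint says 12 months, and that handling of re-treatment is usually left to the analysis plan, which is not shown. The protocol also leans towards counting such a man: the primary objective speaks of residual or recurrent disease after the combination and names no month, other biopsies are admissible, and re-treatment is recorded and reported.

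Part of this stands. The month error has no measurable effect on the primary proportion, and a repeat FT after the 12-month biopsy cannot change that endpoint. The shares in the working are assumed, there is no success rule to inflate, and imputing missing biopsies as positive pulls the other way. It does not dispose of the point. An analysis plan cannot repair instructions to sites. On classification the protocol is not silent: it makes the use of other biopsies discretionary, and leaning towards a reading does not fix it.

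A reader might infer three stronger things that the documents do not support:

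- *A routine 6-month biopsy masks a large share of failures.* The calendar schedules none. A for-cause biopsy on the PSA route needs testosterone recovery, a rise of at least 2 ng/mL over nadir and normally an mpMRI, and the repeat FT must then precede month 12.
- *The re-ablated reading differs from the quantity behind the 30% benchmark.* The protocol gives no source for the 30% and does not say how re-treated men were counted in it.
- *Every early positive biopsy should count as a failure.* That goes beyond the gap and costs power. If it added 0.5–1% of men as positives (assumed), power at a true 15% would fall from 77.3% to 74.0–70.7% at ≤9/51.

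**Conclusion.** The point holds in two parts. The conflict over the month, and over the tissue that triggers a repeat FT, is certain from the text and goes beyond a clerical slip, because it directs cores and response assessment to a biopsy that is not scheduled. The classification gap is also in the text: a man re-ablated for CSPCa before month 12 with a negative 12-month MRI-TB can be counted as CSPCa-free.

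The direction of the bias is known (downward); its size is not. Under the assumed shares it is about 0.2 to 1.5 of 57 men, or 0.3 to 2.6 percentage points at a true 30%, and it is probably small. The probabilities in the working only illustrate, since the protocol fixes no cutoff; they do not show that the trial's error rate is inflated. The correction is worth making because it is cheap and removes a discretionary decision about the primary endpoint.

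**What to change.** 1. Change 6-month MRI-TB to 12-month MRI-TB in Peripheral Blood or Tissue, item 4 of the ablation-template principles, Assessment of Disease and the ninth calendar footnote. Delete the 6-month mark in the correlative-biopsy row. In item 4, extend the trigger to ablated or unablated tissue, to agree with the post-FT section.

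2. Add to the post-FT section and to Study Design/Endpoints: *A man who has a repeat FT or whole-gland treatment for biopsy-proven CSPCa (GG ≥2) before the 12-month MRI-TB counts as positive for the primary endpoint. The site of the positive biopsy assigns him to endpoint 1 or 2, whatever a later biopsy shows.* State that men with an early positive biopsy and no re-treatment remain classified by the 12-month MRI-TB, and that the optional use of other biopsies may not override either rule.

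**Cost.** Amendment wording only. Biopsy sites and re-treatment are already recorded, and the sample size stays at 51/57. The reported CSPCa rate may be slightly higher than if such men were counted as clear: under the assumed shares, 0.3 to 2.6 percentage points at a true 30% and 0.15 to 1.3 at a true 15%. At a true 15% the chance of meeting at most 11/57 is then 86.2%, against an apparent 86.9–91.6% with masking; for at most 9/51 it is 77.3%, against 78.2–84.6%. That gives up only an apparent gain from masking.

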## Post-Focal Therapy Treatment Efficacy/Surveillance mpMRI and MRI-TB

At 12-months from the time of FT, a SOC mpMRI and MRI-TB will be performed to determine treatment response. Both the imaging study and prostate biopsy results will be used to measure efficacy of the proposed combination treatment. However, if a patient has any other post-treatment biopsy results these may also be used to assess for post-treatment efficacy even if not performed with an mpMRI guided biopsy.

Specifically, an MRI-TB will sample the ablated and unablated prostate tissue to determine if residual CSPCa (GG ≥2) remains in the treated and/or untreated prostate tissue. The mpMRI used for the MRI-TB will follow the same imaging protocol as the pre-treatment study and reported in the same manner. Documentation of the biopsy site(s) will be required. If a new suspicious radiographic lesion(s) is/are detected on the subject’s 12-month mpMRI which was/were not present in the pre-treatment [screening] mpMRI then the targeted biopsy cores of the suspicious area(s) will be obtained. Otherwise, if no suspicious lesions are noted in the 12-month mpMRI then random biopsies from the unablated prostate tissue will be obtained per SOC during the MRI-TB.

- Two 18-gauge biopsy cores will be collected from the ablated area(s) and one each from periablation zone and untreated prostate for biobanking and exploratory outcomes on correlatives.

If the 12-month MRI-TB identifies the presence of CSPCa in the ablated or unablated prostate tissue then the patient will be offered a second treatment with FT (if eligible for such treatments) and the follow-up visits for the re-treatment will be the same as the primary treatment. The patients will stay in the study and will continue to be followed up until 12-months from the first FT procedure. For patients with residual/recurrent cancer who decline or are ineligible for a second FT procedure, one of the whole gland treatments, either radical prostatectomy, whole gland ablation or radiation therapy, will be offered. These data will be recorded as part of report of secondary outcomes. Patients who choose to undergo whole gland treatment during the study follow-up will exit the study at this point. HRQOL surveys, PSA and testosterone levels will be obtained at the exit.

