## Multiparametric Magnetic Resonance Imaging 8-weeks Post-ADT Start & Identifying Focal Therapy Disease Targets

After ADT treatment have been initiated, it is anticipated that there will be a decrease in prostate volume due to this combination drug regimen. A change in prostate volume can affect the specific spatial location of a prostate lesion, and the lesion site may have reduced in volume or change morphologically in an unpredictable pattern (see Appendix B for imaging protocol). Ultimately, this study phenomenon can affect FT planning.

To identify if there have been any significant shifts in the size and or location of the previously identified prostate lesion(s) (as compared to the subject’s screening MRI-TB), due to the subject’s potential response to ADT. An additional mpMRI will be performed at 8-weeks after initiation of ADT but prior to FT. This 8-week mpMRI will be compared against the index mpMRI imaging used for eligibility into the study. This additional prostate mpMRI, similar to the mpMRI used for screening, is a radiologic non-invasive investigation.

This research specific 8-week (2-month) post-ADT mpMRI is necessary to ensure the treatment plan during FT is accurate, and also provides the best data to characterize the response to the proposed drug combination.

Pre-operative and all post-operative mpMRI imaging will be performed utilizing the SOC Prostate Imaging Reporting and Data System Version 2.1 (PI-RADS) (see Appendix B for details). Radiologists with expertise in pelvic mpMRI will identify the specified distribution of the lesion(s) and assign a PI-RADS score. Three-dimensional data on the location and specific PI-RADS score for each lesion will be marked by the radiologist and integrated into FT planning.

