# STATISTICAL CONSIDERATIONS

## Study Design/Endpoints

This study will be a multi-institutional single arm phase I/II trial with a recruitment goal of 57 patients with treatment naïve non-metastatic intermediate-risk PCa.

Primary endpoints

1. To determine the proportion of men with CSPCa (GG ≥2) in the ablated prostate tissue by performing a surveillance mpMRI and MRI-TB at 12-months following FT.
2. To determine the proportion of men with CSPCa (GG ≥2) in the unablated prostate tissue by performing a surveillance mpMRI and MRI-TB at 12-months following FT.
3. To demonstrate the safety of combining ADT, and FT for the treatment of men with histopathologic diagnosis of GG 2 & 3 PCa, with PSA level < 20 ng/mL utilizing the NCI’s CTCAE v.5 classification to quantify and characterize the incidence of AEs.

Secondary endpoints

1. To define change in genitourinary and sexual function from baseline following ADT, and FT by measuring the subject’s HRQoL (I-PSS, SHIM, EPIC-26) at 6-and 12-months after FT.
2. To determine the PSA response to the combination treatment by measuring the subject’s PSA at “baseline” (PSA at time of initial diagnosis) and then at 3-months, 6-months, and 1-year from FT.
3. To determine the proportion of men converting to whole gland therapy (radical prostatectomy or radiation therapy) and/or requiring systemic therapy and/or developing metastases and/or dying of PCa during the course of study.
4. To determine the proportion of men without any PCa on any post treatment prostate biopsy.
5. To determine the proportion of men with normal baseline serum testosterone who had testosterone recovery (defined as testosterone levels >300 ng/dL) at 6-, 9- and 12-months after FT.

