## Sample Size/Accrual Rate

It is estimated that the 30% of men who undergo FT for intermediate-risk PCa will have CSPCa (GG ≥2) on repeat biopsy after FT. We hypothesize the combination of ADT, and FT will halve the proportion of men with residual or recurrent CSPCa to 15%. Using sample size estimates for a single proportion, comparing a null proportion of 0.30 to an alternative proportion of 0.15, with an alpha = 0.05 and power at least 80%, the total number of patients required will be 51 men. We estimate 10% attrition for a total sample size of 57 men. We are expecting 18-21 months to enroll all the patients and 36-months to complete the study.

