## Analysis of Primary and Secondary Endpoints

Analysis Populations

Intent-to-Treat (ITT) Population

The ITT population includes all subjects who were enrolled and treated with the combination treatment (ADT (any duration) + FT). Note: Subjects who are enrolled but not treated will be documented as screen failures. The ITT population will serve as the primary analysis set for all safety and efficacy endpoints.

Per Protocol (PP) Population

The PP population includes all subjects who were enrolled and treated with the combination treatment (ADT (any duration) + FT), and who had no major protocol deviations. The PP population will serve as a supportive analysis set for all efficacy endpoints.

Missing Data

The following imputation methods will be used for the primary analysis of all endpoints:

• When calculating the proportion of subjects with a negative biopsy for CSPCa, subjects with missing biopsy information post-ablation will be imputed as “positive”

• Missing PSA data will be imputed using last observation carried forward (LOCF) (or previous median/mean or regression-based methods if proper).

• Missing data for IIEF-5, IPSS and EPIC questionnaires will be imputed using a multiple imputation approach at the item/question level.

All other endpoints/data (e.g., safety events) will be analyzed based on available (non-imputed) data, unless specified otherwise.

Baseline demographic and clinical information will be summarized using standard summary statistics, graphs and charts (see below).

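### Section 8.5 admits any other post-treatment biopsy as efficacy evidence, so a man with only an early negative biopsy may be counted as free of clinically significant cancer at 12 months

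*Protocol*

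**What the plan says.** Protocol section 13.1 (Study Design/Endpoints) sets two efficacy primary endpoints: the proportions of men with CSPCa (Grade Group 2 or higher) in ablated and in unablated tissue. Each is determined "by performing a surveillance mpMRI and MRI-TB at 12-months following FT". The study calendar gives that visit a window of plus or minus 4 weeks.

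Section 8.5 (Post-Focal Therapy Treatment Efficacy/Surveillance) confirms that the 12-month biopsy will be done, then adds that "any other post-treatment biopsy results these may also be used to assess for post-treatment efficacy even if not performed with an mpMRI guided biopsy".

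Under Missing Data in section 13.6, "subjects with missing biopsy information post-ablation will be imputed as" positive. The trigger is the absence of biopsy information after ablation, not the absence of the 12-month MRI-TB.

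On size, section 13.4 sets a 30% null rate against 15% and concludes that "the total number of patients required will be 51 men"; "We estimate 10% attrition for a total sample size of 57 men".

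**The concern.** Read together, the three provisions leave a gap. A man biopsied a few months after FT with a negative result, who never has the 12-month MRI-TB, does have post-ablation biopsy information. On a plain reading he is not imputed positive, and section 8.5 allows his early result to be used.

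An early positive is sound evidence of failure. An early negative cannot exclude CSPCa by month 12, which is the primary question. Nor need an off-schedule biopsy sample both ablated and unablated tissue, although these are separate primary endpoints. Because section 8.5 is permissive and the trial is single-arm, the choice of biopsy could also be made after results are known. Where a negative is substituted, the error favours the hypothesised halving of the rate.

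**Working it through.** **1. The plan's own figure.** Inputs from section 13.4: p0 = 0.30, p1 = 0.15, alpha 0.05 (sidedness not stated), power at least 80%.

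n = [z_alpha·√(p0(1−p0)) + z_beta·√(p1(1−p1))]² / (p0−p1)²

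- One-sided: [1.645·√0.21 + 0.842·√0.1275]² / 0.15² = 49.4, so 50, close to the stated 51.
- Two-sided: 63.9, so 64, which does not match.
- Attrition: 51/0.90 = 56.7, so 57, as stated.

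I therefore work one-sided. The protocol gives no decision rule. With 57 men, the largest count whose exact binomial probability under 0.30 is at most 0.05 is 11 positives: type I error P(X ≤ 11 | 57, 0.30) = 0.049, power P(X ≤ 11 | 57, 0.15) = 0.862.

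**2. Timing.** One 3-month ADT course starts at baseline, and FT follows at 8 to 12 weeks. A biopsy 13 weeks after FT (a hypothetical date) falls at weeks 21 to 25, which is 9 to 13 weeks after 12 weeks of nominal coverage ends. The testosterone-recovery endpoint in section 13.1 is first judged 6 months after FT. Section 8.6 (For Cause Tests) takes the PSA nadir only after recovery to non-castrate testosterone. Such a biopsy may thus fall during testosterone recovery. This is an inference, because the protocol gives no length of carry-over. The section on the 8-week mpMRI says that under ADT "the lesion site may have reduced in volume or change morphologically in an unpredictable pattern", but that concerns imaging for treatment planning, not grade detection at biopsy, and supports the inference only weakly.

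**3. Effect on the estimate.** Let k of 57 men have only an early negative. The protocol gives no k. I take 3 and 6, the latter close to its 10% attrition figure.

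- Bias against the truth, if these men carry a true rate p and the early biopsy detects none of it: (k/57)·p.
- Distance between scoring them negative and imputing them positive: k/57.

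| k | Bias at p = 0.30 | Bias at p = 0.15 | Distance from imputation |
|---|---|---|---|
| 3 | 1.6 points | 0.8 points | 5.3 points |
| 6 | 3.2 points | 1.6 points | 10.5 points |

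At a true 30% with k = 6, the expected reported rate is 0.30·51/57 = 26.8% if they are scored negative, and (0.30·51 + 6)/57 = 37.4% if imputed positive.

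**4. Effect on error rates.** Success is at most 11 positives of 57. The other 57−k men are binomial at the true rate. If the k men are scored negative, success needs X ≤ 11 among 57−k; if imputed positive, X ≤ 11−k.

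| k | Type I, all scored negative | Type I, all imputed positive | Power at 15%, all scored negative | Power at 15%, all imputed positive |
|---|---|---|---|---|
| 0 | 0.049 | 0.049 | 0.86 | 0.86 |
| 3 | 0.078 | 0.008 | 0.90 | 0.58 |
| 6 | 0.121 | 0.0006 | 0.93 | 0.20 |

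**The case against.** **Substitution is not stated.** Section 8.5 says other biopsies may also be used, directly after providing for the 12-month MRI-TB, and the histology table in section 13.6 is headed by that biopsy. The sentence also has a natural home in secondary endpoint 4, which concerns any post-treatment biopsy. A reader might infer that the protocol replaces the 12-month biopsy with whatever biopsy is available; it does not say so. This stands as a limit on wording, but nothing bars the substitution, and the missing-data rule lets it take effect.

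**Early biopsies may be few.** The PSA-triggered for-cause route needs a rise over a nadir taken after non-castrate recovery, which makes biopsy under castration by that route unlikely. An mpMRI is normally required first. Both points stand. Biopsy on clinical suspicion, however, carries no testosterone condition, and section 8.5 expressly accepts biopsies without MRI guidance. References to a 6-month MRI-TB or correlative biopsy also remain in the ablation principles, Assessment of Disease and the study calendar with its footnotes; these need reconciling with the 12-month schedule.

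**The net direction is not fixed.** For-cause biopsies select men under suspicion, so counting them may add positives. True; the concern is confined to negatives.

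**Windows and precedence often belong in the SAP.** That is fair for detail. Here the protocol itself grants a permission at odds with its endpoint definition.

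**Conclusion.** The point holds as a gap between sections 8.5, 13.1 and 13.6: as written, a man with only an early negative biopsy may be counted as CSPCa-free at 12 months. It touches the primary result and should be closed before data accrue.

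Its size rests on an assumed 3 to 6 affected men. Bias against the truth is then at most about 1.6 to 3.2 points at a 30% rate. That is an upper bound, since it supposes the early biopsy detects nothing. A reader might set the 10.5 points against the planned 15-point effect and call most of the effect spurious. That does not follow: 10.5 points is the distance from a worst-case imputation, and it assumes a group as large as the whole attrition allowance had an off-schedule negative biopsy. What the figures do show is that the reading chosen can decide the conclusion, with type I error of 0.078 to 0.121 on one reading and 0.008 to 0.0006 on the other, against a nominal 0.049. Carry-over of ADT is a supporting inference; the point stands without it. The sample size is not in question here.

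**What to change.** - **Section 8.5.** State that, for the primary endpoints, a post-FT biopsy showing Grade Group 2 or higher at any time up to the 12-month assessment counts as positive. A negative counts only from the 12-month assessment biopsy. Other negative biopsies may inform secondary endpoint 4 only.
- **Section 13.6.** Tie the imputation to a missing 12-month biopsy instead of missing post-ablation biopsy information.
- **Sensitivity analysis.** Men whose 12-month biopsy fell slightly outside the 4-week window, or was done without MRI guidance (for example after a new contraindication to MRI), should be handled in a reported sensitivity analysis and not imputed positive automatically.

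The cost is a few sentences, with no new procedure and no change to the 51 and 57. The real price is that some men move from negative to imputed positive. The observed rate becomes less favourable and, at a true rate of 15%, power falls from 0.86 to about 0.58 with three such men and 0.20 with six. That makes completing the 12-month biopsy the main protection.
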